## What is the planned recruitment rate?

The IWK Health Centre NICU admits on average 70 sets of twins per year. Ste. Justine Hospital has a similar admission rate, averaging 80 sets per year. Recruitment rates for similar trials previously conducted in these units have ranged from 55-80%. Given a conservative recruitment rate of 60%, and expected later start date at Ste. Justine Hospital (within 6 months of initial enrolment at the IWK Health Centre), anticipated length of time for recruitment for the study is 12-15 months.

## Will compliance be a concern?

We have conducted a previous pilot study [76] and are conducting a larger clinical trial examining twin regulation during co-bedding over an extended period of time and have not encountered issues related to compliance. Given the short duration of data collection (during one heelstick procedure), we do not anticipate problems with compliance. Nevertheless, we will monitor compliance to group allocation through daily observation and direct staff communication.

## What is the proposed type and frequency of analysis?

Analysis and inference will be based on the intention-to-treat principle. Efforts will be made to ensure that follow up is complete for all subjects and that there are no missing values for any of the subjects for any variable. Blinding of independent coders will be retained until after the analysis is completed. Baseline characteristics of study subjects will be contrasted to ascertain that randomization has in fact produced comparable groups with respect to all variables that effect pain response and physiologic stability. The primary outcome of interest will be the pain response of the infant experiencing a tissue breaking procedure while co-bedding with his/her twin when compared to a twin infant experiencing a tissue breaking procedure receiving standard care (alone in incubator or crib). This analysis will compare the means in the two groups before and after treatment and contrast the mean difference between groups using 95 percent confidence intervals and a p value. The stratified nature of the randomization will be accounted for in the analysis. Also, since twin pairs will be randomized together (i.e. to co-bedding or standard care), the analysis will be corrected for potential non independence of outcomes between twin pairs This will involve appropriate variance adjustment which will be carried out using Generalized Estimating Equations (GEE) procedures using SAS software (Proc Genmod, SAS 8.2, SAS Institute Inc. Cary, NC) [77]. If differences are noted in baseline characteristics, inferences will be made based on observed and (linear regression) adjusted differences between groups. Analysis for secondary outcomes will be done in an identical fashion as pain response and recovery by comparing the mean changes in the two groups before and after treatment and contrasting the mean differences between groups using 95 percent confidence intervals and a p value.

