We based our PIPP score assumptions on previous studies which reported PIPP scores of 10.7 (2.3) vs. 12.9 (2.5) from a study on kangaroo skin-to skin care versus incubator care in preterm infants 32-36 weeks of gestational age [61] and PIPP scores 8.9 (*CI *7.9-9.9) versus 10.7 (*CI *9.6-11.8) in preterm infant 28-31 6/7 weeks of gestational age. Based on these reported 0.5 and 0.6 standard deviation pain scores [66] and the reported values in the above studies, we used a conservative standard deviation estimate of 2.0 as our proposed study population will encompass both groups of infants. Sample size was calculated using a 2-sided alpha error of 0.05 and a power of 80 percent. We designed the study to detect a difference of 1 point or greater change (SD 2.0) in the PIPP scores. One hundred and twenty-eight infants would be required to identify this variation in the PIPP scores if such a difference is in fact caused by co-bedding. With this sample size, we will also have over 95% power to detect a greater than 15 second mean difference in physiological recovery (heart rate and oxygen saturation) between groups. In a recent study of skin-to-skin care [66], the time to return to baseline heart rate following the application of the plaster signifying the end of the procedure was significantly different, 123 seconds (*CI *103-142) for the Kangaroo Mother Care condition and 193 seconds for Incubator condition (*CI *158-227, *p *< .00001). Since all infants will receive 24% sucrose, we do not expect that the differences seen in time to recovery will be this large. Therefore, by using the larger sample, and conservatively accounting for the use of regression techniques, our study will recruit 128 participants (64 sets of twins, 32 assigned to the co-bedding group and 32 to the standard group).

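### The GEE correction for pairing names no small-sample step, with only 64 twin pairs: under the usual sandwich variance and z test, the stratified nominal 5% test would reject about 6.2% to 6.5% of the time under no effect

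*Protocol article*

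**What the plan says.** The Sample Size section plans "128 participants (64 sets of twins, 32 assigned to the co-bedding group and 32 to the standard group"). The section on type and frequency of analysis recognises the clustering, "since twin pairs will be randomized together (i.e. to co-bedding or standard care"), and promises to correct for it by "appropriate variance adjustment which will be carried out using Generalized Estimating Equations (GEE) procedures using SAS software", naming Proc Genmod in SAS 8.2. It says that the stratified randomisation (site and gestational age) will be accounted for. It gives no working correlation, no choice between empirical and model-based variance, no reference distribution and no small-sample correction.

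The next sentence deals with baseline imbalance. If differences are seen, "inferences will be made based on observed and (linear regression) adjusted differences between groups". It does not say whether the pair correction carries over to the adjusted differences. Secondary outcomes are to be analysed in the same way as the primary outcome.

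**The concern.** Both twins of a pair receive the same allocation, so the treatment effect is estimated between pairs. The sample that governs the precision of the standard error is therefore 64 pairs, not 128 infants.

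GEE inference with an uncorrected sandwich variance and a normal reference is a large-sample method. With few clusters the sandwich is biased downwards, because it uses fitted residuals, which are smaller than the true errors. The normal reference also ignores the uncertainty in the variance estimate. Each additional model term (site, gestational stratum, baseline covariates) makes the understatement worse.

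Confidence intervals would then be somewhat too narrow and p values somewhat too small, for the PIPP contrast and for the secondary outcomes that follow the same route. A false claim of a co-bedding effect would be more likely than the stated 5%. A second exposure lies in the adjusted analysis, which is used exactly when the groups look imbalanced: if it were fitted to infants without the pair correction, the error would be larger.

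**Working it through.** **Inputs from the protocol.** Two-sided 5% significance level and 80% power; a target difference of 1 PIPP point with SD 2.0; 64 pairs, 32 per arm; allocation by pair; permuted blocks of 2, 4 or 6 within two sites and two gestational strata.

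**Assumptions.** The within-pair correlation (ICC) is not given; values of 0.1, 0.3 and 0.6 were used for the GEE checks. The number of baseline covariates is not given; 1 to 4 were tried. Scores are taken as normal and strata as near equal in size.

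**Step 1: the plan's own figure.** For two independent means, n per arm = 2 × (1.96 + 0.842)² × 2.0² / 1² = 62.8, so 63 per arm and 126 in total. With 64 per arm the power is 0.807. The stated 128 is reproduced.

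**Step 2: arm only, exact.** With 32 pairs per arm and two infants per pair, the uncorrected sandwich divides each arm's sum of squares of pair means by 32 where the unbiased estimate divides by 31. The standard error is therefore multiplied by √(31/32) = 0.984. A z test on this standard error has size 2 × P(t₆₂ > 1.96 × 0.984) = 5.8%.

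**Step 3: the models that the protocol describes.** Null rejection rate of the uncorrected sandwich with |z| > 1.96, by simulation (20,000 runs at infant level with exchangeable GEE, 40,000 at pair level with the protocol's blocks; Monte Carlo error about 0.12 to 0.19 points):

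| Model | Null rejection | SE relative to true SD |
|---|---|---|
| Arm only (exact) | 5.8% | 0.98 |
| Arm + site + gestational stratum | 6.2% to 6.3% | 0.96 to 0.97 |
| Arm + four stratum levels | 6.4% to 6.5% | 0.96 |
| Strata + 1 to 2 covariates | 6.6% to 7.2% | 0.93 to 0.96 |
| Strata + 4 covariates | about 7% to 7.5% | about 0.93 |

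Varying the ICC from 0.1 to 0.6 made almost no difference. Scores rounded and clipped to 0 to 21 gave 6.5%. If 30% of pairs have only one infant measured, the stratified model gave 6.1%.

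**Step 4: other tests under the same GEE fit, arm plus strata.** Model-based SE with z, 5.5% to 5.9%. Score test, 5.4% to 5.6%. Uncorrected sandwich with a t reference, 5.6% to 5.9%. All are closer to 5%, and all are still above it.

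**Step 5: the corrected version.** Each squared pair residual is divided by (1 − leverage), and the statistic is referred to t on (pairs − parameters) degrees of freedom. Rejection was 4.9% to 5.2% in the pair-level scenarios, including those with covariates. A stronger leverage correction with t, tried in the infant-level runs, was conservative, at 3.6% to 4.8%.

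**Step 6: adjusted regression without the pair correction.** With two infants per pair, the true variance of a between-pair contrast is (1 + ICC) times the one that ordinary regression assumes. Size = 2 × [1 − Φ(1.96 / √(1 + ICC))]:
- ICC 0.1: 1.96 / √1.1 = 1.869, size 6.2%
- ICC 0.3: 1.96 / √1.3 = 1.719, size 8.6%
- ICC 0.5: 1.96 / √1.5 = 1.600, size 11.0%

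**The case against.** The strongest objection is that the protocol does not say that it will use the empirical variance or a normal test. It promises an appropriate variance adjustment by GEE. The variance option, degrees of freedom and any small-sample correction are details that an analysis plan commonly settles, and that plan is not shown. The article identifies the pair as the unit of allocation and names a standard method, so nothing in it is plainly wrong. This stands in part: the figures for the uncorrected sandwich are conditional on an option that the document leaves open. It does not remove the point, because the other GEE tests checked with strata also exceed 5% (5.4% to 5.9%), and the remedy changes the named method to a better one.

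A reader might infer that the primary test itself rejects 6.5% to 7.5% of the time. The documents do not support that. The stratified model gives about 6.2% to 6.5%. The higher values need several extra covariates, which the protocol adds only if baseline differences are noted, and then reports beside the observed difference.

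A reader might also infer from the words about linear regression that the adjusted analysis drops the pair correction. That reading is possible but is not the natural one. The preceding sentences say that the analysis will be corrected for pairing, and GEE for a continuous score with an identity link is a linear regression. The 8.6% and 11% therefore show why the wording should be made explicit. They do not describe what the plan says it will do, and they rest on assumed correlations.

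**Conclusion.** The point holds in a limited form. The protocol relies on a large-sample correction for a contrast between 32 and 32 pairs and names no small-sample step. If the uncorrected sandwich with a z test is used, type I error is about 5.8% with arm only, about 6.2% to 6.5% for the stratified analysis described, and about 7% to 7.5% with around four added covariates. The excess for the described primary analysis is thus about 1.2 to 1.5 percentage points. It could decide a borderline result but would not overturn a clear one.

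The conclusion rests on normal scores, near-equal strata, all 64 pairs contributing, and the assumption about the variance option. It hardly depends on the within-pair correlation, except for an adjusted regression that ignored pairing. It does not show that the planned intervals and p values are certainly wrong. This is a cheap improvement to the analysis section, not a flaw in the design.

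**What to change.** Keep the pair as the cluster and name a small-sample method for the unadjusted and adjusted analyses alike. Either of these will do:
- GEE with a bias-corrected sandwich variance and a t reference on (pairs − parameters) degrees of freedom. Name the correction: dividing squared pair residuals by (1 − leverage) held the size near 5% here, while a stronger version was conservative.
- A linear mixed model with a random pair effect and Kenward-Roger degrees of freedom.

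Add one sentence saying that the regression-adjusted differences come from this same pair-clustered model, and apply it to the secondary outcomes too.

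The cost is one or two sentences and a slightly wider interval. As a guide, the width changes by about (t quantile / 1.96) × √(64 / (64 − p)), where p is the number of parameters:
- arm only (p = 2): 1.999 / 1.96 × √(64/62) = 1.036, about 4% wider
- arm, site and gestational stratum (p = 4): 2.000 / 1.96 × √(64/60) = 1.054, about 5% wider
- four stratum levels plus four covariates (p = 9): 2.004 / 1.96 × √(64/55) = 1.103, about 10% wider

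No extra infants, staff or design change are needed.

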## Trial management

The principal investigator will assume the role of study coordinator as part of the requirements of her PhD studies. She will be responsible for the day-to-day management of the trial at the IWK Health Centre. An experienced research nurse will assume the role of coordinator and responsibilities at the IWK during any absences by the principal investigator. A research nurse, having weekly contact with the principal investigator, will coordinate and oversee data collection at the Ste. Justine site.

## Expected contributions

A number of clinical and theoretical contributions are expected from this study. First, it is anticipated that the results from this study will contribute to evidence-based research in the field of pain in preterm neonate health, specifically as it relates to co-bedding and developmentally sensitive care practices. If twin contact while co-bedding is determined to have a positive effect then changes in current neonatal care practices to include co-bedding for twins may be an inexpensive, non-invasive method to minimize preterm twin infant pain during painful procedures. Additionally, the role of a twin in the care of his co-twin may be clarified with this study. As it was stressed in the review of literature, very little is known about the short or long term contribution that a twin can make through their continued presence with their co-twin during hospitalization. Utilizing the practice of co-bedding as an intervention to reduce pain in their preterm newborn can add to our understanding of the potential strength of the relationship between twins. Additionally, given the increased incidence of multiple gestation births and admission of these high risk infants to neonatal units, if co-bedding is found to be beneficial it may raise further questions regarding the need for possible differences in care of twins and higher order multiples versus singletons in the NICU setting.

Theoretically, this area of research is important because there is an increasing realization that alleviation of pain among infants is critical for healthy growth and long-term development. This research will clarify the role of co-bedding and provide at-risk infants with comfort that will facilitate their optimal growth and development. Data will provide valuable information to help better understand the mechanisms contributing to increased comfort within a multisensorial context. Lastly, the results of this study will provide valuable insight into the relationship between twins - whether they are able to provide comfort to each other. Data from the response of the co-twin as an exploratory question will also address this relationship.

## Potential risks to the safety of participants involved in the study

### a. Co-bedding condition

All twins will have continuous cardio-respiratory monitoring and ongoing surveillance for any adverse effects. If a co-bedded infant shows clinical signs of sepsis, twins will be separated until sepsis has cleared. If the incidence of co-infection among co-bedded twins increases significantly above the unit norm, the trial will be discontinued.

### b. Confidentiality

Confidentiality of all data collected will be maintained. All information gathered would be coded before analysis and data will be stored in a secure, locked location accessible only to the principal investigator and research nurse. The list of code numbers and names will be stored separately from the coded data. When the study results are published or presented at a health care conference, the information shared will not contain any personal identifiers. The salivary cortisol samples, coded with a number will be kept frozen in a locked freezer located at the IWK Health Centre and St. Justine NICU until it is couriered in batches for analysis at the McGill University laboratory. Cortisol samples will not be used for any other purpose. All videotapes will be encrypted. Master copies of research data will be kept secure in a locked location until five years past the age of majority of the infants.

## Ethics

Authorization and informed consent will be obtained from a parent(s) of eligible twins prior to study entry. The IWK Health Centre, Ste. Justine Hospital and McGill University Research Ethics Board have approved this study. The principal investigator or site research nurse will explain the research study to the parents if twins meet the study criteria. Parents will read the Consent/Authorization Form and any questions they may have concerning the research study will be answered. The Consent/Authorization form will contain information on potential risks and benefits to the participants, research rights of the participant, and information on how to contact the invetigator or study nurse. Participation in the study will be voluntary. Parents will be made aware of their right to withdraw their children at any point in the course of the study. Consent forms will be provided in English or French and a copy will be provided to participants once signed.

Co-bedding is considered to be a safe practice for twins. Nevertheless, a careful watch will be kept on all study participates with regard to any possible adverse effects of co-bedding. Infants will be monitored as per the NICU Care Unit standard of care and their clinical condition will be evaluated daily as part of medical rounds and by the study team. Heelstick procedures are an aspect of usual care for infants in the NICU and will not be conducted solely for the purpose of this study. Study participation will not interfere with routine care practices. Routine strategies for pain relief including sucrose administration and non-pharmacologic measures will be provided as per standard IWK Health Centre NICU care.

Co-bedding twins is not considered to be a standard of care in the NICU. This study provides no direct benefit for the parents or infants enrolled. Compensation will not be offered. There will be no study restrictions regarding the continued practice of co-bedding until 48 hours prior discharge for those infants allocated to the co-bedding group

## Study timeline

The initial preparation time for this study will be two weeks. During that time, information will be given to the staff of the NICU regarding study protocol. A second site (Ste. Justine) will commence recruitment within 6 months of initiation in the first site (IWK Health Centre). Subject accrual and data collection will extend over 12-15 months. It will take an additional 4 months to analyze the data and prepare a manuscript. The study results will be widely disseminated through conference proceedings and peer reviewed publication. The total duration of the study is expected to be 20-24 months.

## Discussion

All staff and parents will be informed that we are co-bedding twins while in the NICU for the purposes of research only. We do not intend for this research to indicate support of co-bedding after discharge. Since there is currently little research completed to support the benefits or risks of co-bedding, this will remain a parental decision. We will recommend that parents follow the back-to-sleep program and refrain from smoking regardless of which ever sleep arrangements they choose.

## Dissemination Plan

The design and scientific merit of this study will provide data that will be applicable to like populations within Canada and elsewhere. The generation of further knowledge in this area will help in the formulation of evidence-based recommendations for vulnerable infants experiencing procedural pain and the role of developmental care practices. This program of research has significant implications for the health of hospitalized at-risk infants, both short and long-term. Ongoing research is aimed at identifying optimal developmental strategies that may lessen the adverse effects of procedural pain. Findings will be communicated locally to front line care providers from multiple disciplines, families and administrators to facilitate uptake of knowledge and generate policy change directly affecting patient outcomes. Changes in practice and outcomes will be communicated via best practice networks to stimulate uptake nationally. The research findings also have worldwide relevance in the area of neonatal care and will be communicated nationally and internationally in peer-reviewed journals, conference proceedings and via consultation with community interest groups (Parents of multiple birth association (POMBA) and related networks (worldwide twin neonatal group-Vermont Oxford Network).
